#### Protocol Feasibility

We will undertake a preliminary study in our center before conducting the full-scale research project. It will take at least 3–4 months (including an enrolment period of about 3 months) to recruit ~15 patients and 15 healthy people as controls. We aim to address current uncertainties regarding the feasibility of sampling and parameters. If at least 80% of patients have valid and complete data of the MUL-GM-CSCPB study Data Recording Sheet (Supplementary Table), the pilot study will be successful and data from the pilot phase will be included into the final analysis. Some modifications will be made in the protocol if it is hard to reach the criteria. Data from the pilot phase will be included into the final analysis if no modification has been made.

### Experimental Analysis

#### Metagenomic Analysis

We chose metagenomics for sequencing studies of intestinal microecology. The metagenomics data will be annotated by comparing the predicted genes with the non-redundant protein sequence (NR) database. The metagenomic annotations provide comprehensive species information, including not only bacteria but also fungi, archaea, and viruses. First, DNA extraction will be performed using commercial kits according to the manufacturers' instructions. Libraries will be constructed according to a commercial kit and sequenced using the paired-end method and 93 cycles of sequencing. After read processing, we will perform taxonomic annotation according to related software. We will search every identified sequence from the UniProt/Swiss-Prot database (18) and subsequently retrieve the protein family, KEGG orthologous group and pathway information (19) associated with each UniProt/Swiss-Prot accession number. The relative proportion of read counts will be used as a quantitative estimation of the abundance of each taxon or function. We will keep the metagenomic sequence data on an open access site.

#### Metabolomics Analysis

The blood and stool samples will be analyzed using untargeted metabolomics. The analysis will be performed on an ultra-high-performance liquid chromatography system. To detect as many metabolites as possible, we plan to perform both polar ionic and lipid modes depending on the properties of the serum metabolites. The raw data will be converted into mzXML format and then processed by XCMS (20) software for peak picking and alignment. Metabolite features generated from XCMS will be further quantified by metaX software (21), including missing value imputation, data filtering, normalization, and comparison. Significant metabolites will be calculated using univariate (T/Wilcoxon test) and multivariate (PCA and PLS-DA) analyses integrated in metaX. The online HMDB database (22) and KEGG database (19) will be used to annotate the polar ionic metabolites by matching the exact molecular mass. The MS/MS spectrum from HMDB, MassBank (23) and an in-house database will assist in metabolite identification. For lipid identification, a LipidBlast database (24) will be used by matching the MS/MS spectrum and retention time. MetaboAnalyst (25) will be used for the identification of metabolic pathways.

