#### Sample Collection

There will be 60 patients enrolled as the case group and 30 healthy people as the control. After fasting for at least 6 h but not more than 10 h, venous blood will be collected by direct venepuncture or established venous access from patients enrolled. Plasma will be taken from the blood and remain in Eppendorf tubes at −80°C for 1 h. Fresh fecal samples will be obtained (sometimes aided by glycerinum) and stored at −80°C before analysis. In the control group, samples will be collected once. In the case group, feces and blood samples will be acquired at the following time points (Figure 1): (1) T1: 1 day before cardiac operation; and (2) T2: within 24–72 h of ICU admission, sampling must be performed before patients start oral feeding.

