#### Observation and Data Recording

Demographic data describing age, sex, main diagnosis, and past medical history are available at the inception of the study. Data related to the CPB time and application of antibiotics post-operation are available on the MUL-GM-CSCPB study Data Recording Sheet (Supplementary Table). The following observational data will be measured and recorded when patients are admitted to the ICU and at every sampling time.

Sequential (sepsis-related) organ failure assessment includes blood pressure; mean arterial pressure (MAP); and vasoactive drugs, including noradrenaline (NE), epinephrine (E), and dopamine (Dopa); PaO_2_/FIO_2_; Glasgow Coma Scale score; creatinine or urine output; bilirubin; and platelet count.Infection-related items include body temperature, WBC count, neutrophils, PCT, and antibiotics.Whether to be diagnosed with sepsis (according to Sepsis 3.0).Infection site and pathogenic microorganism.Nutrition and gastrointestinal function assessment including enteral or parenteral nutrition, bowel dilatation tested by ultrasound, gastric residual volume and intra-abdominal pressure measured via bladder.

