#### Definition

The clinical criteria according to the third international consensus (Sepsis-3) (17):

Sepsis: suspected or documented infection and an acute increase of ≥2 SOFA points.

Suspected infection group will be identified as those who had body fluids sampled for culture and received antibiotics but had a negative culture result.

The documented infection group will be identified as those who had body fluids sampled for culture with a positive result.

Survivors: Patients that survive for 28 days or more after surgery.

Non-survivors: Patients that survive <28 days after surgery.

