### Multi-Omic Data Analysis Plan

The data will be analyzed according to the case and control groups, sepsis and non-sepsis groups, and survivor and non-survivor groups, or some other classifications based on the pathophysiology.

Metagenomic and metabolomics statistical analysis will be performed using commercial software. To account for dependencies in repeatedly measured observations within a subject, a linear mixed-effect model will be used to assess the differences between the case group and the control group. Statistical analysis will be performed using SPSS (version 22, SPSS, Chicago, IL). A two-sided significance level of 0.05 will be used for statistical inferences. Combining principal component analysis (PCA), partial least squares discriminant analysis (PLS-DA), and orthogonal partial least square discriminant analysis (OPLS-DA), different metabolite profiles will be identified.

Receiver operating characteristic (ROC) analysis will be conducted to evaluate the utility of the potential biomarkers selected. Multivariate logistic regression analysis will be used to show the correlation between each factor and prognosis and changes in intestinal flora. A *p* < 0.05 will be considered statistically significant.

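### In the post-operative plasma comparison of sepsis with non-sepsis, creatinine and bilirubin help define the groups and can also be selected as biomarkers (partial incorporation bias)

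*Protocol article*

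**What the plan says.** All references are to the protocol article.

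- **Label.** The section Definition gives "Sepsis: suspected or documented infection and an acute increase of ≥2 SOFA points".
- **SOFA inputs.** Observation and Data Recording lists the scored items, among them "creatinine or urine output; bilirubin; and platelet count".
- **Timing.** The same section states: "The following observational data will be measured and recorded when patients are admitted to the ICU and at every sampling time". Sample Collection sets the post-operative sample as "T2: within 24–72 h of ICU admission". The SOFA items and the T2 plasma therefore describe the same time.
- **Candidate features.** Metabolomics Analysis says "The blood and stool samples will be analyzed using untargeted metabolomics", and describes the breadth as follows: "To detect as many metabolites as possible, we plan to perform both polar ionic and lipid modes depending on the properties of the serum metabolites".
- **Selection.** The same section continues: "Significant metabolites will be calculated using univariate (T/Wilcoxon test) and multivariate (PCA and PLS-DA) analyses integrated in metaX".
- **Use.** Multi-Omic Data Analysis Plan names sepsis versus non-sepsis as one of the groupings and then says "Receiver operating characteristic (ROC) analysis will be conducted to evaluate the utility of the potential biomarkers selected".

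No section says that a metabolite which is itself a SOFA item is removed, flagged or reported separately.

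**The concern.** A marker judged against a reference standard that contains it will look better than it is. Here a high creatinine or bilirubin earns SOFA points, and SOFA points are required for entry to the sepsis group. If the same molecule is then screened for a difference between the groups, some of the difference comes from the way the groups were formed.

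This matters because the Introduction asks whether post-operative fever with hemodynamic instability reflects sepsis or a purely inflammatory response. The non-sepsis group mixes patients without organ dysfunction and patients with organ dysfunction but no infection. A label component can separate the groups while saying nothing about infection, and would then be listed as a biomarker with an ROC curve beside it.

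**Working it through.** The plan gives no figure on this point, so there is none to reproduce. The check asks how far creatinine separates the groups when it has no relation to infection.

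**Inputs from the article:** 30 septic and 30 non-septic patients (Study Design), a Wilcoxon test (Metabolomics Analysis), two-sided level 0.05 (Multi-Omic Data Analysis Plan), and sepsis as infection plus a SOFA rise of at least 2 (Definition).

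**Assumptions not in the article:** all infection and organ-scoring rates, and infection independent of the organ scores.

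**Step 1, formula.** Let q be the proportion infected, S the proportion with a SOFA rise of at least 2, and A the AUC of creatinine for a SOFA rise of at least 2 against a smaller one. Septic patients have the creatinine distribution of all SOFA-high patients. Non-septic patients are a mixture: a share (1−S)/(1−qS) is SOFA-low, and a share S(1−q)/(1−qS) is SOFA-high without infection. Against the second share the AUC is 0.50. Hence

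AUC (sepsis v non-sepsis) = 0.5 + (A − 0.5) × (1 − S)/(1 − qS).

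The excess over 0.50 comes entirely from the SOFA-low comparators and vanishes as S approaches 1.

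**Step 2, six SOFA organs, q = 0.40.** S and A come from simulation of 200,000 patients. The organ rates are the assumed probabilities of at least 1, 2 and 3 points, and rho is the latent correlation between organs.

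| Setting | S | A | AUC by formula | p<0.05 at 30 v 30 |
|---|---|---|---|---|
| All organs 35/15/5%, rho 0 | 0.785 | 0.663 | 0.5 + 0.163 × 0.215/0.686 = 0.551 | 11% |
| All organs 20/10/3%, rho 0.5 | 0.381 | 0.834 | 0.5 + 0.334 × 0.619/0.848 = 0.744 | 92% |
| Two organs 90/60/30%, other four 35/15/5%, rho 0 | 0.985 | 0.665 | 0.5 + 0.165 × 0.015/0.606 = 0.504 | 5% |
| Two organs 90/60/30%, other four 20/10/3%, rho 0.5 | 0.888 | 0.815 | 0.5 + 0.315 × 0.112/0.645 = 0.555 | 10% |

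The AUCs simulated directly were 0.550, 0.743, 0.504 and 0.557, so the formula holds. Repeat runs move the last column by one or two percentage points: the six-equal-organ settings have given 11% to 94%, with AUC 0.55 to 0.75, and the settings with two commonly scoring organs 4% to 12%, with AUC 0.50 to 0.56.

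**Step 3, a second model.** With four independent components and 30% to 90% infected, creatinine's AUC was 0.54 to 0.73 with p<0.05 in 7% to 87% of comparisons. Bilirubin's AUC was 0.53 to 0.65 with p<0.05 in 6% to 54%. Against infection status alone, creatinine's AUC was 0.50.

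**Step 4, the cleaner contrast.** In the six-organ model, creatinine in septic patients against non-infected patients with a SOFA rise of at least 2 had an AUC of 0.50 in every setting.

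**The case against.** **Silence in a condensed article.** The list of eligible biomarkers could be settled in a fuller plan, and Metabolomics Analysis does mention a data-filtering step. This has some weight. But the article itself fixes the label, the sampling time, the feature set and the path to ROC, and together these create the overlap. The general filtering step is not described as removing label components.

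**Inferred candidates.** The article does not name creatinine or bilirubin as measured metabolites. That stands as a limit: the inference rests on an untargeted assay of plasma for small molecules. Urine output may also supply the renal points instead of creatinine, and the label requires infection as well. The incorporation is therefore partial.

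**Size.** Where two organ systems commonly score after bypass, nearly all patients reach the SOFA threshold, infection then drives the label, and the bias almost disappears. This stands. The simulations also treat the level of creatinine as the score, while the definition asks for an acute increase.

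**Two stronger readings.** A reader might infer that every metabolite tracking kidney or liver function merely restates the label. The documents do not support that. Such metabolites are not SOFA inputs, and organ dysfunction is part of what the article means by sepsis, so an association with it is not in itself an artefact. A reader might also infer that the planned logistic regression is circular because SOFA items and antibiotics are among the recorded factors. Multi-Omic Data Analysis Plan relates its factors to prognosis and changes in intestinal flora, and does not name sepsis as the outcome.

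**Conclusion.** The point holds in a narrow form. In the T2 plasma comparison of sepsis with non-sepsis, creatinine and bilirubin are label components and, by inference, candidate features, so the plan as written can credit either as a sepsis biomarker partly because it defines the group. With no true link to infection, the direction is upward, but the size rests wholly on assumed rates: creatinine's AUC from about 0.50 to 0.75, and p<0.05 in about 5% to 94% of comparisons of 30 with 30. The upper figures should not be read as what this study will see.

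The point does not extend in the same way to the T1 samples, the metagenomic data, the comparison with healthy controls or 28-day survival. It is a modest but worthwhile correction to one secondary comparison.

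**What to change.** In Metabolomics Analysis and Multi-Omic Data Analysis Plan, add two statements.

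1. Creatinine, bilirubin and their direct annotated derivatives are excluded from biomarker selection and ROC for sepsis versus non-sepsis. Alternatively, they are reported but flagged as components of the sepsis definition that are not eligible as biomarkers.
2. For the candidates that remain, the contrast of septic patients with non-infected patients whose SOFA rose by at least 2 is reported as a sensitivity analysis. It should not be a condition for calling a feature a sepsis marker, because that would replace the declared contrast with a different question.

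Both use data already recorded and need no further patients or samples. The cost is a few lost features and an extra comparison that will be small and imprecise; the article does not allow the size of its comparator group to be predicted.

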### Multi-Omic Data Analysis Plan

The data will be analyzed according to the case and control groups, sepsis and non-sepsis groups, and survivor and non-survivor groups, or some other classifications based on the pathophysiology.

Metagenomic and metabolomics statistical analysis will be performed using commercial software. To account for dependencies in repeatedly measured observations within a subject, a linear mixed-effect model will be used to assess the differences between the case group and the control group. Statistical analysis will be performed using SPSS (version 22, SPSS, Chicago, IL). A two-sided significance level of 0.05 will be used for statistical inferences. Combining principal component analysis (PCA), partial least squares discriminant analysis (PLS-DA), and orthogonal partial least square discriminant analysis (OPLS-DA), different metabolite profiles will be identified.

Receiver operating characteristic (ROC) analysis will be conducted to evaluate the utility of the potential biomarkers selected. Multivariate logistic regression analysis will be used to show the correlation between each factor and prognosis and changes in intestinal flora. A *p* < 0.05 will be considered statistically significant.

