## Method and Analysis

### Study Design

This protocol is designed as a prospective observational case–control study in patients who underwent cardiopulmonary bypass (CPB) due to cardiac surgery. Thirty healthy persons aged between 18 and 85, without digestive system disease, will be selected as the control group. The case group will include patients admitted to the intensive care unit (ICU) after cardiac surgery with CPB, which is performed by the Department of Cardiac Surgery of Peking Union Medical College Hospital. The patients enrolled should be divided into two groups according to their outcomes: one group of non-sepsis patients and the other group of sepsis patients after cardiac surgery. Sample collection will be terminated when each group receives 30 cases. These 60 cases will be regarded as the case group. Additionally, all the patients we observe will be further divided into survivors and non-survivors based on 28-days survival. Feces and blood samples will be obtained at certain time points (Figure 1).

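### Biomarkers are selected and then scored by ROC in what appears to be the same small sample, with no correction for optimism, so the reported AUC would be biased upward

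*Protocol article*

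**What the plan says.** The relevant steps are in two sections of the protocol article.

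- **Selection (Metabolomics Analysis).** The data are untargeted, and the stated purpose of the assay modes is "To detect as many metabolites as possible". Then: "Significant metabolites will be calculated using univariate (T/Wilcoxon test) and multivariate (PCA and PLS-DA) analyses integrated in metaX".
- **Further selection (Multi-Omic Data Analysis Plan).** PCA, PLS-DA and OPLS-DA are combined: "orthogonal partial least square discriminant analysis (OPLS-DA), different metabolite profiles will be identified". The threshold is unadjusted: "A two-sided significance level of 0.05 will be used for statistical inferences".
- **Evaluation (same section).** "Receiver operating characteristic (ROC) analysis will be conducted to evaluate the utility of the potential biomarkers selected".
- **Contrasts (same section).** Case vs control, sepsis vs non-sepsis, and "survivor and non-survivor groups, or some other classifications based on the pathophysiology".
- **Subjects.** Study Design, on the sepsis and non-sepsis groups: "Sample collection will be terminated when each group receives 30 cases". Sample Collection: "There will be 60 patients enrolled as the case group and 30 healthy people as the control". Study Setting describes one center. Protocol Feasibility moves the pilot data into the final analysis if the pilot succeeds without protocol changes.
- **Purpose.** The text under Figure 1 in Study Design promises predictive biomarkers as an output.

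The article mentions no hold-out set, external cohort, cross-validation, permutation test or optimism correction.

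**The concern.** ROC analysis is meant to show how well a marker separates patients who were not used to choose it. Here the markers reach the ROC step because they separated the groups in the data at hand. PLS-DA and OPLS-DA go further, since they build a direction that separates the labelled groups. If the same patients are then used for the ROC curve, chance separation is counted as discrimination. The effect grows with the number of candidate features and shrinks with the number of patients, and this study has many features and few patients.

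What is at stake is the predictive-biomarker output. The bias acts in one direction only, and its size depends on feature count and panel size, so a reader given the apparent AUC alone cannot tell how much of it is signal.

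**Working it through.** **Plan's own figure.** There is none to reproduce. The article gives no expected AUC, effect size or sample-size derivation; 30/30/30 are fixed counts.

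**Inputs**
- Group sizes: 30 vs 30 for sepsis (Study Design); 60 vs 30 for case vs control (Sample Collection).
- Significance level: 0.05 two-sided, unadjusted (Multi-Omic Data Analysis Plan).
- Number of features p: not stated. Assumed 100, 500, 1,000 and 5,000, independent of each other.

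**Analytic check, 30 vs 30.** The null standard error of one AUC is √[(n₁+n₀+1)/(12·n₁·n₀)] = √[61/(12×30×30)] = √(61/10,800) = 0.075. A single marker passes p<0.05 once its AUC exceeds about 0.5 + 1.96×0.075 = 0.65. Under the null, 0.05×p markers pass: 5, 25, 50 and 250 for the four values of p. Every one of them arrives at the ROC step with an AUC of at least about 0.65; in simulation they average about 0.67.

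**Simulation of pure noise, 30 vs 30.** Features are standard normal and unrelated to outcome, with 100 data sets per setting (40 at p=5,000). Entries are mean AUCs. The first three result columns are scored in the same patients used for selection and fitting.

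| p | Best single marker (5th–95th percentile) | Ten-marker logistic panel | PLS-DA, 1 component | Top 5, selected once on all 60, model fit cross-validated | Top 5, selection inside 5 folds | PLS-DA, 2 components, fitted inside 5 folds |
|---|---|---|---|---|---|---|
| 100 | 0.70 (0.66–0.76) | 0.92 | 0.97 | 0.79 | 0.51 | 0.51 |
| 500 | 0.74 (0.71–0.77) | 0.97 | 1.00 | 0.85 | 0.49 | 0.50 |
| 1,000 | 0.75 (0.72–0.79) | 0.98 | 1.00 | 0.86 | 0.49 | 0.51 |
| 5,000 | 0.78 (0.75–0.81) | 0.995 | 1.00 | 0.91 | 0.51 | 0.49 |

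A separate run gave 0.89–0.98 for a ten-marker score over the same range of p, and 0.47–0.53 with selection and fitting inside the folds. The ten-marker result is therefore best read as about 0.89–0.99, depending on how the markers are combined.

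**What the columns show**
1. Single-marker ROC is clearly inflated above 0.5, but moderately.
2. A panel or a PLS-DA score looks excellent to perfect under pure noise.
3. Cross-validating only the final model does not help (0.79–0.91), because the selection has already seen every patient.
4. Repeating selection and fitting inside the folds removes the bias.

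**Case vs control, 60 vs 30, same method.** Best single marker 0.68–0.75; ten-marker logistic panel 0.87–0.97; two-component PLS-DA 0.99–1.00.

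**Survivor contrast, illustration only.** The Introduction cites 3% in-hospital mortality in another cohort; 0.03×60 = 1.8, about 2 deaths. The best single noise marker then averages 0.96–1.00. With 6 deaths (an assumption, since this sample is enriched for sepsis) it averages 0.83–0.93.

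**The case against.** **The article is condensed, and a full protocol or SAP may specify validation.** That is possible, and silence on the number of folds or components would be no finding. But these sections are not silent on the procedure. They name the tests, the projections, the significance level and the evaluation method, in an order that biases the result if followed as written. The criticism is of that sequence.

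**The article never says the same patients are used.** Correct. It is an inference, though a sound one: recruitment stops at the stated numbers, no second cohort is described, and the one subset that could have been kept apart is pooled.

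**A reader might infer that noise alone gives a near-perfect AUC whatever is done.** The documents do not support that. They do not say whether ROC is applied marker by marker or to a combined score. For single markers in sepsis vs non-sepsis the best noise marker averages 0.70–0.78, and its 95th percentile is 0.81 even at 5,000 features, so a clearly higher AUC would stand out. Near-perfect values need a panel, a PLS-DA score, or the survivor contrast with very few deaths.

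**Other points that stand.** The ROC contrast is not named, and case vs control uses 90 subjects, not 60. The selection tests are stated for metabolites only; no rule is given for metagenomic features. Real features are correlated, so the effective p may lie near the low end, but the inflation is present at p=100. The wording is partly exploratory, which tempers the consequence but does not remove the bias from an AUC reported as utility.

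**Conclusion.** The point holds in this form: the procedure as written gives AUCs that are biased upward and cannot by themselves support a claim of predictive biomarkers. With no true signal at 30 vs 30, the apparent AUC averages about 0.70–0.78 for the best single marker, 0.89–0.99 for a ten-marker panel and 0.97–1.00 for a PLS-DA score, against about 0.5 when selection and fitting are repeated inside the folds.

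This rests on three assumptions: that selection and ROC use the same subjects (inferred), that there are 100–5,000 candidate features (not stated), and that features are independent (a simplification). It does not show that the study has no real signal. It shows that the apparent AUC would not reveal whether there is one.

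**What to change.** In the Multi-Omic Data Analysis Plan, after the ROC sentence, state that:

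1. Biomarker utility will be reported as an optimism-corrected AUC with a confidence interval. It will come from nested cross-validation or from a bootstrap in which filtering, selection, PLS-DA/OPLS-DA fitting and any cut-off are redone in every resample. Either method serves.
2. Each PLS-DA/OPLS-DA model will carry a label-permutation p value (for example, 1,000 permutations).
3. The apparent AUC may be shown beside the corrected one, but not alone as evidence of utility.

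It would also help to say which contrast the ROC analysis serves and whether it is applied to single markers or to a combined score, since the size of the bias depends on both.

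The cost is analysis time and lower reported AUCs. No further patients or samples are needed.

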**Figure 1 F1:**
[figure not shown]
Study design.

The fecal sample analysis will apply metagenomics, and the feces and blood samples will be analyzed using an untargeted metabolomics method. We intend to explore the stratification of gut microbial communities in patients who underwent cardiac surgery with CPB and to analyze the variation in metabolites in patients' plasma and fecal samples. Predictive biomarkers and possible pathogenesis of FUO and hemodynamic instability after CPB will also be provided by clinical outcome analysis combined with a multi-omics study.

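### Biomarker utility rests on ROC analysis with no reference named, although PCT, WBC and neutrophils are recorded at the same sampling times, so a marker that largely tracks them may appear useful

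*Protocol article*

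**What the plan says.** The Study Design section of the protocol article sets a biomarker aim: "Predictive biomarkers and possible pathogenesis of FUO and hemodynamic instability after CPB will also be provided by clinical outcome analysis", combined with the multi-omics work. The Multi-Omic Data Analysis Plan then gives the method for judging the markers: ROC "analysis will be conducted to evaluate the utility of the potential biomarkers selected". It names no comparator, base model or AUC difference. It also does not say whether the curves are for single markers or a combined panel, or which of the study's groupings they use.

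The same section adds one multivariable model: "Multivariate logistic regression analysis will be used to show the correlation between each factor and prognosis and changes in intestinal flora". Its covariates are not listed.

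Observation and Data Recording lists the routine infection data: "Infection-related items include body temperature, WBC count, neutrophils, PCT, and antibiotics". These items "will be measured and recorded when patients are admitted to the ICU and at every sampling time", so they coincide with the patients' omics samples. The Definition section defines sepsis as suspected or documented infection with a SOFA rise of at least 2 points. PCT, WBC and neutrophils are not named in it.

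**The concern.** The ICU already has PCT, WBC and neutrophils. Whether a new marker is useful there depends on what it says beyond them, and an ROC curve without a reference does not address that.

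The gap matters in this study because the Introduction asks whether fever and haemodynamic instability after bypass reflect sepsis or a purely inflammatory response, and the Discussion says bypass itself provokes systemic inflammation. Routine infection markers and plasma metabolites may both respond to that inflammation. A metabolite that largely tracks PCT could then separate the sepsis group from the non-sepsis group and be put forward as a biomarker while telling the clinician little that is new. Correcting for the selection of markers on the same data would not cure this, because a marker can discriminate genuinely and still be redundant.

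At stake is the secondary biomarker claim, not the primary comparison of patients with healthy controls.

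**Working it through.** The protocol gives no AUC target, effect size or power for the biomarker step, so there is no figure to reproduce. What follows is an illustration of size.

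**Inputs from the protocol**
- Group sizes 30 and 30: "Sample collection will be terminated when each group receives 30 cases" (Study Design).
- Two-sided alpha 0.05: "A two-sided significance level of 0.05 will be used for statistical inferences" (Multi-Omic Data Analysis Plan).

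**Assumptions (not in the protocol)**
- PCT is normal with unit variance in each group, with an AUC for sepsis of 0.75 (range 0.70 to 0.85).
- The marker is M = r × PCT + √(1 − r²) × noise, with within-group correlation r of 0.5, 0.7 or 0.9. By construction it carries nothing once PCT is known.
- The ROC result is judged by a test of AUC = 0.5. The protocol does not state this test; it is used here as the usual reading of a significant ROC.

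**Step 1: the marker's own AUC.** The PCT group difference is d = √2 × z(0.75) = 1.414 × 0.6745 = 0.954. The marker's difference is r × d, and its AUC is Φ(r × d/√2) = Φ(r × 0.6745).
- r = 0.5: Φ(0.337) = 0.63
- r = 0.7: Φ(0.472) = 0.68
- r = 0.9: Φ(0.607) = 0.73

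**Step 2: how large an AUC is significant at 30 v 30.** The null standard error is √[(30 + 30 + 1)/(12 × 30 × 30)] = √(61/10,800) = 0.075. The threshold is 0.5 + 1.96 × 0.075 = 0.65, so the redundant marker's true AUC lies near or above it.

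**Step 3: chance that the redundant marker is significant on its own ROC.** Rank test, simulated, PCT AUC 0.75:

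| r | Own ROC significant | Added to a PCT model (likelihood-ratio test) |
|---|---|---|
| 0.5 | 41–43% (two independent simulations) | about 5–6% |
| 0.7 | 69% | about 5% |
| 0.9 | 87% | about 5% |

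Normal-approximation check at r = 0.7: r × d = 0.668, the standard error is √(2/30) = 0.258, the ratio is 2.59, and Φ(2.59 − 1.96) = 73%. This is slightly above the simulated rank test, as expected.

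Over PCT AUC 0.70–0.85 and r 0.5–0.9, the own-ROC rate runs from 25% to about 100%, and the added-value test stays at about 5–6%. That second figure is simply the test's nominal level, since redundancy was built in.

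**Step 4: power of the added-value test when a marker truly adds information.** Same group sizes, PCT AUC 0.75, simulated:

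| Marker AUC | Within-group r with PCT | Power |
|---|---|---|
| 0.68 | 0.3 | 28% |
| 0.75 | 0.5 | 50% |
| 0.75 | 0.7 | 30% |
| 0.80 | 0.5 | 82% |

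A non-significant added-value test at this sample size is therefore weak evidence that a marker is redundant.

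**The case against.** The strongest reply is that the article is condensed, that a reference marker is the kind of detail an unseen analysis plan may fix, and that ROC analysis of candidate markers is not in itself wrong. All of that is fair. It limits the point to this: the visible text links utility to ROC analysis and names no benchmark, although the data for one are collected.

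The logistic regression might also supply the comparison, since PCT and WBC could be among its factors. But its stated targets are prognosis and change in flora. Nothing ties it to the ROC step or to gain over routine markers.

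Three limits stand.
- The benchmark does not suit every grouping. The protocol describes no PCT or WBC for healthy controls. At T1, patients with preoperative fever or anti-infective treatment are excluded, so preoperative values are plausibly a weak guide to later sepsis. The comparison fits sepsis versus non-sepsis at T2.
- PCT and WBC are not wholly independent of the outcome label. Suspected infection is defined by cultures taken and antibiotics given, and PCT or WBC may prompt both. That could flatter the benchmark.
- The study is also about mechanism. A marker on a path from flora through inflammation to sepsis may share PCT's signal and still be informative, so overlap with PCT is no reason to discard it.

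A reader might infer that the plan tests each marker's own curve against 0.5 and that a copy of PCT is bound to be reported as useful. The text supports neither: it states no null value, threshold or curve type, and the chance of a significant curve depends on unknown quantities.

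**Conclusion.** The point holds in a limited form. Utility rests on ROC analysis with no reference named, while suitable routine markers are recorded at the same times, so a marker that largely tracks them may appear useful. At an assumed PCT AUC of 0.75 the illustrated risk is about 41–43% at r = 0.5 and 69% at r = 0.7. These figures depend on the assumed AUC and correlation, on PCT as the only routine marker, and on a test of AUC = 0.5. They show that the problem could be sizeable, not how often it will occur.

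It might seem to follow that a marker should count as useful only if it adds significantly to PCT and WBC. That does not follow, because such a rule would often reject markers that truly add information. The comparison is worth making as something to report beside the ROC result.

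**What to change.** For sepsis versus non-sepsis with T2 samples, add to the Multi-Omic Data Analysis Plan:

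- Name PCT and WBC from the same sampling time as the reference, and report their AUCs beside that of each marker or panel put forward.
- Report the AUC difference with its confidence interval, and a likelihood-ratio test of the marker added to a logistic model with PCT and WBC fixed in advance. Keep antibiotics and SOFA components out of that model, since they help define sepsis.
- Limit any claim of utility beyond routine tests to what this comparison supports. Do not use the test as a pass/fail rule for keeping a marker.
- State as a limitation that PCT and WBC may influence the suspected-infection label through the decision to culture and give antibiotics.

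The cost is one extra model per marker, on data already recorded. With 60 patients the AUC difference will be imprecise, and the utility statement will probably be less favourable than one from ROC curves alone.
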